#### Secondary analyses

The same analysis described above will be conducted for the change from baseline in percentage of adherent days from months 2 to 6 in order to analyse the trajectory of adherence change induced by the intervention. All months will be simultaneously analysed and standard errors will be adjusted for individual clustering. Next, logistic regressions of indicator variables indicating whether the 75 % and 90 % adherence goals are achieved will be estimated from months 2 to 6. Regressors will include the study arm, a variable indicating whether the adherence goal was achieved at baseline, change in number of daily doses taken and the same baseline characteristics as for the primary analysis.

Changes from baseline in IOP and GQL-15 and EQ5D-5 L scores at month 6 will be linearly regressed on the study arm, their baseline values, and the same other baseline characteristics as for the primary analysis. If the intervention shows improvements (relative to the control group) both in terms of GQL-15 and EQ5D-5 L scores, we will conduct an economic analysis using utilities derived from the change in EQ5D-5 L score. The costs will be obtained from the financial incentives paid during the last month of the trial and from assumptions on operational and administrative costs incurred if the intervention were to be scaled up. The perspective of the analysis will be that of a governmental agency subsidizing healthcare costs.

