### Outcome measures

#### Primary outcome

Our primary outcome is the *mean change from baseline in percentage of adherent days at month 6*. A day will be counted as adherent when the patients take all their medication(s) within the appropriate dosing windows for the day. The percentage of adherent days during month 1 (baseline) and month 6 will be calculated for each patient and the difference in mean change between study arms will be tested. The primary outcome is directly incentivized in the VP arm and not incentivized in the UC arm. As a result, this outcome will appropriately capture the behavioural change induced by value pricing, if any.

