### Sample size

We chose to power the study to detect differences of ten percentage points in average monthly percentage of adherent days at 6 months between the two study arms. This effect size is sufficient to measure the effects reported by a majority of financial incentive studies [30] and is in line with a recent study that also used percentage adherence measured by electronic caps as primary end point [43]. In order to detect such effect size, a total of 100 participants is needed. This calculation assumes a two-sided statistical test of difference in means with a 5 % significance level and a power of 80 %. In addition, the standard deviation of the monthly percentage of adherent days is assumed to be no greater than 16.3 %, which is the maximum standard deviation in dose-rate adherence reported by Robin and colleagues [44]. Finally, attrition over the 6-month study is assumed to be no greater than 20 %.

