### Statistical methods

#### Primary analysis

Change from baseline in percentage of adherent days at month 6 will be linearly regressed on the (i) study arm (VP vs. UC), (ii) baseline percentage of adherent days, (iii) change in number of daily doses taken in order to correct for potential medication change or number of eCAPs™ tracked, and (iv) other baseline characteristics (age, language spoken, income, IOP, BIPQ and BMQ scores) in order to increase statistical efficiency. The linear model will be estimated via ordinary least squares (OLS) and the hypothesis of equality between the mean change in primary outcome between the study arms will be tested by testing whether the binary variable indicating the study arms equals zero using a *t* test. All tests will be bilateral, performed at the 5 % level of statistical significance, and carried out using the statistical software Stata version 13.1 (StataCorp LP, College Station, TX, USA).

The analysis will be performed according to an intention-to-treat approach. If multiple medication users have faulty devices, adherence will be calculated based on functioning devices. Remaining missing adherence data will be imputed using Markov chain Monte Carlo multiple imputation including as predictors all factors mentioned above. In addition, for sensitivity analysis, baseline adherence will be carried forward for patients who withdraw from the study as those VP patients who do not achieve their goals might disproportionally withdraw from the study.

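### The 75% and 90% goal-attainment models appear to adjust for a yes/no baseline indicator rather than the continuous baseline percentage, at a small cost in efficiency

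*Protocol article*

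**What the plan says.** Under Secondary analyses the protocol article plans "logistic regressions of indicator variables indicating whether the 75 % and 90 % adherence goals are achieved will be estimated from months 2 to 6". The regressors are the study arm, "a variable indicating whether the adherence goal was achieved at baseline", and "change in number of daily doses taken and the same baseline characteristics as for the primary analysis".

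Under Primary analysis the linear model has four items: (i) the arm, (ii) the "baseline percentage of adherent days", (iii) the change in daily doses, and (iv) "other baseline characteristics (age, language spoken, income, IOP, BIPQ and BMQ scores) in order to increase statistical efficiency". Baseline adherence is item (ii) and is not in the list at (iv).

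The continuous value is available, because the Primary outcome section states: "The percentage of adherent days during month 1 (baseline) and month 6 will be calculated for each patient". No reason is given for using a dichotomy in the logistic models.

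**The concern.** The logistic regressor list follows the order of the primary model's items (i) to (iv), with a yes/no indicator where item (ii) stood. For the 75% goal, that indicator treats a patient at 10% of adherent days at baseline like one at 74%, although their chances of reaching 75% later would be expected to differ. The plan's stated reason for its other baseline covariates is efficiency, and prior adherence is a natural predictor of later adherence.

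At stake is some power on two secondary outcomes that mirror the rebate thresholds. For the 90% goal there is a further practical point: if few patients meet it at baseline, the indicator hardly varies and can do little as a covariate.

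**Working it through.** **Inputs from the Sample size section.** The aim is to "detect differences of ten percentage points in average monthly percentage of adherent days at 6 months between the two study arms"; SD 16.3, two-sided 5%, power 80%, 100 patients, attrition up to 20%. Allocation is 1:1.

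**The plan's own figure first.** n per arm = 2 × (1.96 + 0.8416)² × 16.3² / 10² = 2 × 7.849 × 265.69 / 100 = 41.7, so 42 per arm and 84 in total. Inflation by 1.2 gives 84 × 1.2 = 100.8, close to the stated 100 (84 / 0.8 would give 105). With 100 × 0.8 = 80 completers, 40 per arm: 10 / (16.3 × √(2/40)) = 2.744, and Φ(2.744 − 1.96) = 0.783. These figures concern the continuous primary outcome; no power is stated for the logistic models.

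**Assumptions not in the document.** Control mean (equal to the baseline mean) of 60, 70 or 80%; baseline to follow-up correlation of 0.3, 0.5 or 0.7; normal values clipped to 0–100.

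**How informative is the 90% indicator?** The share at goal at baseline is 1 − Φ((90 − mean) / 16.3):
- mean 60%: 1 − Φ(1.84) = 0.03, about 2.6 of 80 patients
- mean 70%: 1 − Φ(1.23) = 0.11, about 8.8 of 80
- mean 80%: 1 − Φ(0.61) = 0.27, about 21.6 of 80

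**Power, single month.** 40 per arm, +10 points in the VP arm, likelihood-ratio test, 1,500 simulated trials per row. Both models were fitted to the same data.

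| Mean | Correlation | 75% goal: indicator → continuous | 90% goal: indicator → continuous |
|---|---|---|---|
| 60% | 0.3 | 0.576 → 0.575 | 0.344 → 0.333 |
| 60% | 0.5 | 0.578 → 0.617 | 0.328 → 0.341 |
| 60% | 0.7 | 0.607 → 0.689 | 0.349 → 0.403 |
| 70% | 0.3 | 0.611 → 0.621 | 0.479 → 0.485 |
| 70% | 0.5 | 0.629 → 0.654 | 0.489 → 0.509 |
| 70% | 0.7 | 0.704 → 0.761 | 0.548 → 0.600 |
| 80% | 0.3 | 0.555 → 0.571 | 0.617 → 0.612 |
| 80% | 0.5 | 0.583 → 0.595 | 0.628 → 0.645 |
| 80% | 0.7 | 0.641 → 0.688 | 0.681 → 0.735 |

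The differences are −1 to +2 points at 0.3, which is within simulation noise, 1 to 4 at 0.5, and 5 to 8 at 0.7. The 60% mean with the 90% goal is the least stable combination: about 3% and 11% reach the goal, or 40 × 0.03 + 40 × 0.11 ≈ 6 events per trial. A longer repeat run gave smaller differences there and the same overall pattern elsewhere.

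**Power, months 2 to 6 pooled.** Month terms, cluster-robust Wald test, mean 70%, correlation 0.3 / 0.5 / 0.7:
- 75% goal: 0.970 → 0.975; 0.955 → 0.985; 0.950 → 0.989
- 90% goal: 0.916 → 0.935; 0.859 → 0.917; 0.831 → 0.934

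Over all pooled scenarios run, the gain is 0.5 to 2 points at 0.3, 3 to 6 at 0.5 and 4 to 10 at 0.7. The 90% goal at a 60% mean was not run pooled.

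**Share of the adjustment gain lost.** At mean 70% and correlation 0.7, unadjusted single-month power is 0.607 (75% goal) and 0.461 (90% goal). The indicator forfeits (0.761 − 0.704) / (0.761 − 0.607) = 37% and (0.600 − 0.548) / (0.600 − 0.461) = 37% of what continuous adjustment adds.

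**Further checks.** With no effect (mean 70%, correlation 0.5, pooled), rejection rates were 0.055 and 0.056 with the indicator and 0.060 and 0.049 with the continuous term. In the single-month runs, using both baseline terms gave about the same power as the continuous term alone. The models omit the other covariates, which could shrink the gain if they correlate with baseline adherence.

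**The case against.** **The text may already include the continuous value.** The logistic sentence refers to the primary model's baseline characteristics without the word *other*, whereas the next paragraph, on IOP and quality of life, keeps that word. On a literal reading, the baseline percentage could sit beside the indicator, and then nothing is lost. This reading is possible but less natural, because the list runs parallel to items (i) to (iv). The ambiguity stands and is itself a reason for a clarifying sentence.

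**The indicator is a coherent choice.** The outcome is defined as change from baseline in the proportion meeting each threshold, and the indicator is the baseline value of that same binary outcome. That stands: the choice is conventional and does not contradict the primary model. Randomisation, however, does not require the baseline covariate to share the outcome's form.

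**The loss may be very small.** This also stands. The document gives no correlation, and at 0.3 there is practically no loss. In the pooled 75% analysis at mean 70%, power is at least 95% with either term.

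**A reader might infer that most of the value of adjustment is lost, or that separation will make the 90% model unusable.** The documents support neither. The share forfeited was 37% in the two cases worked above. Low baseline attainment is an inference: patients are selected on a self-reported scale, and no electronic-cap distribution is given. Empty baseline-by-outcome cells arose in 45 to 65% of single-month simulations, but only for the 90% goal at an assumed 60% mean (at most about 5% at 70%). An empty cell makes the indicator's coefficient diverge, and software may drop those patients, but the arm effect generally remains estimable.

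**Conclusion.** The point holds as a modest loss of efficiency on two secondary outcomes. As most naturally read, the logistic models use a dichotomised baseline where the continuous one is available. The cost in power is about nil at correlation 0.3, a few points at 0.5, and roughly 4 to 10 points at 0.7 across the single-month and pooled analyses. These sizes rest on assumed correlations and means; the SD, effect size and number of completers are the protocol's.

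It should not be read as a bias, a type I error problem or an internal contradiction. The primary analysis is untouched, since it already adjusts for the continuous baseline, and no power is claimed for the goal-attainment models. Severity is minor: a cheap improvement.

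**What to change.** State in Secondary analyses that the logistic models for both goals adjust for the continuous month-1 percentage of adherent days, either replacing the goal indicator or added beside it. If it was always meant to be included, the same sentence removes the ambiguity.

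The cost is one covariate, using data already collected. There is a small downside: the continuous term assumes linearity on the logit scale, and the arm odds ratio becomes conditional on a different covariate, so its value is not interchangeable with that from the indicator model. The choice should therefore be fixed before outcome data by arm are examined.

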### Objectives

*Primary objective*: determine whether complementing usual care (UC) with adherence-contingent rebates according to a VP strategy is superior to UC alone in improving medication adherence between baseline and month 6.

*Secondary objective 1*: determine whether the IOP of patients in the VP arm improves more (or deteriorates less) than that of patients in the UC arm between baseline and month 6.

*Secondary objective 2*: determine whether the glaucoma-related (GQL-15) and generic health-related (EQ5D-5 L) quality of life of patients in the VP arm improves more (or deteriorates less) than that of patients in the UC arm between baseline and month 6.

*Secondary objective 3*: determine whether the incremental cost-effectiveness ratio (ICER) of VP compared to UC will be favourable relative to international benchmarks for cost-effectiveness.

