### Study arms

In this study, patients learn about their arm allocation by phone 1 month after their enrolment. This is to collect 1 month of baseline data on medication adherence. The patients then remain in their respective study arm for a duration of 5 months. In both arms, a questionnaire and clinical assessment will take place at baseline and month 6.

During the baseline visit, the research optometrist takes note of the glaucoma medication dosing schedule (see Fig. 1) in the participant instruction booklet (see Additional file 1) to ensure a uniform presentation of adherence goals across participants. Medication adherence will be monitored during the whole 6-month period by means of electronic containers eCAPs™ (Information Mediary Corporation, Ottawa, ON, Canada). An eCAP™ is a medication event monitoring system with an inbuilt electronic tag which records the time whenever it is opened and closed. Each eye drop will be stored in separate vials with separate eCAPs™. At month 3, eCAPs™ are collected by a courier service, medication adherence is calculated for months 2 and 3 and the eCAPs™ are returned to the patients along with a short adherence report for that period (see Additional files 2 and 3). The next assessment period for medication adherence runs from months 4 to 6, and adherence calculation takes place after the patients returned their eCAPs™ at the month 6 study assessment. Patients also receive a call at the end of months 2 and 5 to verify that they understand their arm allocation and adherence goals, and that patients with multiple eye drops keep their medication in the assigned eCAP™.

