#### Secondary outcomes

*Monthly mean change from baseline in percentage of adherent days at months 2 to 5* in order to monitor adherence trajectories before the study end point (month 6).*Monthly change from baseline in the proportion of patients with percentage of adherent days greater or equal to respectively 75 % and 90 % over the study period (i.e. from month 2 to 6)*. These outcomes are of interest as they are defined according to the adherence thresholds that VP patients need to meet in order to receive their financial incentives.*Mean change from baseline in IOP at month 6*.*Mean change from baseline in GQL-15* [38] *score at month 6* as a glaucoma-specific measure of quality of life.*Mean change from baseline in EQ-5D-5L* [39] *score at month 6* as a generic measure of quality of life.*Mean cost of financial incentives at month 6 in the VP arm. Individual cost of financial incentives will be calculated using the participants’ monthly glaucoma-related healthcare costs recorded at baseline and percentage of adherent days at month 6 (i.e. primary outcome).*

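### The ICER is a secondary objective without conditions, but the economic analysis is run only if VP improves both quality-of-life scores, and incentive cost is defined in more than one way

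*Protocol article*

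**What the plan says.** **The objective.** In the protocol article, Objectives, secondary objective 3 is to "determine whether the incremental cost-effectiveness ratio (ICER) of VP compared to UC will be favourable relative to international benchmarks for cost-effectiveness". No condition is attached.

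**The analysis.** Under Statistical methods, Secondary analyses, the economic analysis has an entry condition: "If the intervention shows improvements (relative to the control group) both in terms of GQL-15" and also EQ-5D-5L. If it is met, "we will conduct an economic analysis using utilities derived from the change in EQ5D-5 L score". GQL-15 does not enter the calculation. The article does not say whether improvement means a favourable point estimate or a significant difference.

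**The incentive cost.** Three descriptions appear:

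- *Study arms* and *Arm 2*: rebates are earned per assessment period. The first period covers months 2 and 3; then "The next assessment period for medication adherence runs from months 4 to 6". Each rebate is based on one visit plus three months of medication, with a floor and a cap on the cost base.
- *Secondary analyses*: "The costs will be obtained from the financial incentives paid during the last month of the trial", to which are added "assumptions on operational and administrative costs incurred if the intervention were to be scaled up".
- *Secondary outcomes*: each VP patient's cost is calculated from "monthly glaucoma-related healthcare costs recorded at baseline and percentage of adherent days at month 6".

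**The concern.** An objective that asks whether an intervention is cost-effective must be able to receive the answer no. Under the condition as written, the clearest negative answer (VP costs more and gains no utility) can never come out of the planned analysis, because the analysis is not run in that case. When it is run, the EQ-5D-5L difference in the ICER's denominator has already been selected for being favourable, so it is too large on average and the ICER looks too good. A third effect is that GQL-15 acts as a veto: EQ-5D-5L may favour VP and still no ICER is produced.

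The cost side raises a smaller question. If the three descriptions are different quantities, two analysts could follow the article and put different numerators in the same ICER.

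**Working it through.** **1. Model for the condition.** Let the estimated VP-minus-UC effects on the two scores, each divided by its SE and signed so that positive favours VP, be bivariate normal with correlation ρ. The documents give no ρ; I assume 0 to 0.5. Working in SE units means that no standard deviation is needed.

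**2. Improvement read as point estimates, no true effect.**

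- P(both > 0) = 1/4 + arcsin(ρ)/(2π)
- Mean EQ-5D-5L effect given both > 0 = (1 + ρ) / (2√(2π)) ÷ P(both > 0)

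For ρ = 0: P = 0.25, and the mean is 0.1995/0.25 = 0.80 SE. For ρ = 0.5: P = 0.25 + 0.5236/6.2832 = 0.333, and the mean is 0.2992/0.3333 = 0.90 SE. Without the condition the mean is 0.

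**3. The same reading with a true effect on both scores (simulation).** The simulation also reproduces the closed-form results in step 2.

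| True effect on both | ρ | ICER run | Mean EQ-5D-5L effect when run | Bias | EQ-5D-5L favours VP but no ICER |
|---|---|---|---|---|---|
| 0 SE | 0 | 25% | 0.80 SE | 0.80 SE | 25% |
| 0 SE | 0.3 | 30% | 0.87 SE | 0.87 SE | 20% |
| 0 SE | 0.5 | 33% | 0.90 SE | 0.90 SE | 17% |
| 1 SE | 0 | 71% | 1.29 SE | 0.29 SE | 13% |
| 1 SE | 0.3 | 73% | 1.33 SE | 0.33 SE | 11% |
| 1 SE | 0.5 | 75% | 1.35 SE | 0.35 SE | 10% |
| 2 SE | 0 to 0.5 | about 96% | 2.06 to 2.07 SE | 0.06 to 0.07 SE | about 2% |

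The last column is the GQL-15 veto.

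**4. Improvement read as both significant** (two-sided 5%, in favour of VP, z > 1.96 on each). The analysis is run in under 0.5% of trials with no effect, in 3% to 7% at 1 SE, and in 27% to 35% at 2 SE.

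**5. Incentive cost.** The article's own range reproduces: 0.50 × 36.50 = SGD18.25 and 0.50 × 240 = SGD120 per assessment period at the 50% rate. For a patient at that rate in both periods:

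- Rebates paid over the two periods: 2 × 18.25 = SGD36.50 to 2 × 120 = SGD240.
- Last-period rebate spread over its three months: 18.25/3 = SGD6.08 to 120/3 = SGD40 per month. Over the five intervention months: SGD30.42 to SGD200.

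At the cap these differ by 240/200 = 1.20, because the first period pays on three months of medication but covers two months of adherence.

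The rebate tier can also differ between month 6 and months 4 to 6. For illustration, with equal months: adherence of 95, 95 and 60% averages 83.3%, which earns the 25% rebate under the period rule and none on month 6 alone. Adherence of 80, 92 and 95% averages 89.0%, which earns 25% under the period rule and 50% on month 6 alone.

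**The case against.** **The ingredients are reported anyway.** GQL-15, EQ-5D-5L and mean incentive cost are secondary outcomes with no condition, and main results are to be published whatever their direction. A careful reader could see that VP cost more without utility gain. This stands as mitigation. It does not answer objective 3, because nobody would report the ICER or its uncertainty, and it does not remove the selection from an ICER that is reported.

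**The bias is largest under no effect.** This also stands. At a true effect of 2 SE on both scores, the point-estimate condition hardly matters. The inability to return a negative answer does not depend on the true effect.

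**The article condenses a fuller plan.** The meaning of improvement may be fixed elsewhere, so its absence here is not the finding. The condition itself is stated, and it conflicts with the objective under either meaning.

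**Is the ICER mis-costed?** A reader might infer this, for example by supposing that a rebate covering a whole assessment period will be entered as one month's cost. No section says so. The Secondary outcomes section works from monthly costs and month-6 adherence, and the Secondary analyses section adds scale-up costs from a government payer's perspective. Together these can be read as a forward-looking steady-state monthly cost, which is a legitimate choice. Nor does the article state a time horizon that such a cost would contradict. What remains is an inconsistency of definition. Paying out per period has its own quirk (the 1.20 ratio in the working), so rebates paid are not self-evidently the better base case.

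**Conclusion.** The point on the condition holds. The objective is unconditional and the analysis is not. As written, the plan cannot report VP as dominated, conditions any ICER on a favourable EQ-5D-5L result, and lets a score outside the ICER block it. The size depends on the meaning of improvement and on the assumed correlation of 0 to 0.5. On point estimates with no true effect, the ICER is run in 25% to 33% of trials, with EQ-5D-5L overstated by 0.80 to 0.90 SE. The bias is about 0.3 SE at a true effect of 1 SE and under 0.1 SE at 2 SE. On significance, the objective goes unanswered in at least 93% of trials for true effects up to 1 SE, and in roughly two-thirds or more at 2 SE.

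On cost, the documents support only that three descriptions need to be reconciled. They do not show that the cost is wrong, or by how much.

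**What to change.** 1. In Secondary analyses, delete the entry condition. Run the cost-effectiveness analysis whatever the direction of the GQL-15 and EQ-5D-5L results, report its uncertainty, and state that VP will be reported as dominated if it costs more without utility gain.
2. In Secondary outcomes and Secondary analyses, use one definition of incentive cost and state its time base, matched to that of the utility gain. A steady-state month-6 monthly cost can be the base case if it is named as such, with rebates actually paid over both assessment periods as the alternative scenario.

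The cost is rewording and a modest amount of analysis. EQ-5D-5L is collected at both visits and rebate amounts are entered on the adherence reports, so no new data are needed. The price is that an unfavourable or very uncertain ICER may have to be published.

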### Study setting and eligibility criteria

All patients will be recruited at the Singapore National Eye Centre (SNEC). Singapore is an island city-state that has a population of 5.5 million and which is one of the most densely populated countries in the world. Singapore is a multicultural country consisting of Chinese (76.2 %), Malay (15 %), Indian (7.4 %) and other (1.4 %) ethnicities. The most widely spoken languages in Singapore are English, Mandarin, Malay and Tamil. The vast majority of those who speak Malay and Tamil are also fluent in English.

SNEC is part of SingHealth, which is Singapore’s largest public healthcare group. Since 1990, SNEC has been providing a full range of high-quality eye care and is a referral centre for complex cases both nationally and internationally. With its research arm, the Singapore Eye Research Institute (SERI), SNEC also extensively engages in academic research. SNEC treats both high-income patients and low-income patients. All Singaporean citizens and permanent residents are entitled to government subsidies in case of referral, while low-income patients can benefit from additional subsidies through various government schemes. The study will be conducted in collaboration with Duke-NUS, which is part of the academic medical centre SNEC belongs to.

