#### Arm 2: value pricing (VP)

The treatment received by VP patients is strictly identical to that received by UC patients, with the only exception being that VP patients can earn rebates on their glaucoma-related healthcare costs contingent on being sufficiently adherent to their medications.

Adherence is measured as the percentage of days where the patients take all their medication(s) within the appropriate dosing windows for the day. According to this definition, if a patient fails to take a single dose during the corresponding window, the whole day is counted as non-adherent. This concept of adherent-day stresses the importance of complying to the medication regimen as a whole and to its schedule in efforts to limit detrimental IOP fluctuations.

Patients who achieve more than 90 % adherent days will receive a rebate amounting to 50 % of their glaucoma-related healthcare costs, and patients achieving between 75 % and 90 % of adherent days will receive a 25 % rebate. Glaucoma-related healthcare costs comprise the out-of-pocket healthcare expenditure of one clinic visit at SNEC and 3 months’ worth of glaucoma medications per assessment period. When calculating glaucoma-related healthcare costs, a lower limit of SGD36.50 (the price of a subsidized doctor visit at SNEC) and an upper limit of SGD240 will be applied for those patients who spend less or exceed these limits. This means that those who qualify for a 50 % rebate will receive a rebate amount comprised between SGD18.25 and SGD120 per assessment period. Note that the rebate amounts will be explained to the patient and written down in the participant instruction booklet by the research optometrist during the baseline visit. However, emphasis will be given to the rebate rate (i.e., 25 % or 50 %) in order to be consistent with a value-based insurance design. Rebate payment is made via ebanking but the amount earned is added on the medication adherence report in order to make it fully visible to the patient.

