Measurement of the primary outcome critically depends on all patients keeping their medication(s) stored in their tracking device(s). This study requirement will be emphasized at recruitment and reiterated during the follow-up calls. The possibility of gaming (i.e. opening and closing the tracking device without effectively taking the medication) has also been considered. While the medication causes little side effects, some patients might want to save on medication costs. In efforts to counter and detect this potential behaviour, participants will be asked to sign a participation oath [46] and their medication purchases will be monitored. During the baseline visit, participants will be asked to keep all their medication bills and bring them to the month 6 visit. Based on the bills and a discussion with the participant, the research optometrist will assess whether the purchases correspond to 6 months of medications. While these measures are not fully fail proof, our strategy is to maximize the chances of receiving unbiased feedback by having this discussion take place after all study payments have been made to the participant and by asking nonthreatening questions on medication purchasing habits during the trial. We apply a similar strategy to verify adherence to the monitoring devices with the research optometrist asking nonthreatening questions on eCAP™ use at the end of the month 6 assessment once all payments have been made to the participant.

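### The ICER takes the view of an agency that subsidises care, but its cost list has no line for a change in subsidised medication or visits; if drops are subsidised and VP increases their use, the ICER is understated

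*Protocol article*

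**What the plan says.** Secondary objective 3 (Objectives) is to "determine whether the incremental cost-effectiveness ratio (ICER) of VP compared to UC will be favourable relative to international benchmarks for cost-effectiveness". The method is in Statistical methods, Secondary analyses. The economic analysis is run only on a condition: "If the intervention shows improvements (relative to the control group) both in terms of GQL-15 and EQ5D-5 L scores". Its cost side has two sources. The first is the rebates: "The costs will be obtained from the financial incentives paid during the last month of the trial". The second is the expense of running the scheme, which is to be derived "from assumptions on operational and administrative costs incurred if the intervention were to be scaled up". The next sentence sets the viewpoint: "The perspective of the analysis will be that of a governmental agency subsidizing healthcare costs".

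Three other places bear on this.

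- **Who is subsidised.** The inclusion criteria admit only citizens and permanent residents. Study setting and eligibility criteria says of that group: "All Singaporean citizens and permanent residents are entitled to government subsidies in case of referral". It names neither medication nor a subsidy share. The one subsidised item named in the protocol is a doctor visit, in the section on the VP arm.
- **What the rebate is based on.** The VP arm section states: "Glaucoma-related healthcare costs comprise the out-of-pocket healthcare expenditure of one clinic visit at SNEC and 3 months’ worth of glaucoma medications per assessment period". Under Secondary outcomes, each patient's incentive cost is computed from monthly costs recorded at baseline and from adherence at month 6.
- **What is known about purchases.** According to the Discussion, "participants will be asked to keep all their medication bills and bring them to the month 6 visit". The stated purpose is to detect patients who open the device without using the drops.

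**The concern.** A cost-effectiveness analysis should count the costs that fall on the payer whose perspective it takes. An agency that subsidises healthcare pays part of each subsidised item. If an intervention changes how much subsidised care is used, that change is part of the agency's incremental cost. Here the intervention aims to make patients take their drops, yet the cost list has no item for medication, visits or any other care.

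The rebate term does not fill the gap. It is a rate applied to a fixed cost recorded at baseline, so it does not move with the drops actually bought, and it covers the patient's share rather than the government's.

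At stake is the comparison with international benchmarks in secondary objective 3. If government-paid use rises more under VP than under UC, incremental cost is too low and VP looks more cost-effective to this payer than it is.

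**Working it through.** **1. The protocol's own figure.** The only incentive amounts stated are for the 50% rebate per assessment period, SGD18.25 to SGD120. From the cost limits in the VP arm section:

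- 0.50 × 36.50 = 18.25
- 0.50 × 240 = 120

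Both match. Divided by 3 for a monthly amount, this is SGD6.08 to SGD40. The protocol gives no ICER and no subsidy figure to reproduce.

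**2. Does the rebate term respond to extra use?** Incentive cost = rebate rate × bounded baseline out-of-pocket cost for one visit and a fixed supply. Adherence enters only through the rate (0%, 25% or 50%). The quantity of drops bought does not enter, and neither does the government-paid share. So the term cannot capture the omitted cost.

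**3. Size of the omitted cost.** Let

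- M = monthly out-of-pocket cost of the full regimen;
- s = share of the full price paid by government;
- e = extra share of the full regimen consumed under VP relative to UC.

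The full price is M/(1 − s), so the government pays M × s/(1 − s) for a full regimen. Then:

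Omitted subsidy per patient-month = e × M × s/(1 − s)

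A 50% rebate on the same drugs is 0.5 × M, so:

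Omitted subsidy / rebate = e × [s/(1 − s)] / 0.5

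The protocol gives none of e, M or s. The values below are assumptions. For e, 0.10 borrows the 10-point difference in the Sample size section, although that difference refers to adherent days and not to doses used. For M, the range is SGD10 to SGD80 per month. The upper value is the rebate cap, 240/3, which also includes the visit.

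| Assumed s | s/(1 − s) | Omitted SGD per month at e = 0.10, M = 10 to 80 | % of 50% rebate, e = 0.05 | % of 50% rebate, e = 0.10 | % of 50% rebate, e = 0.20 |
|---|---|---|---|---|---|
| 0 | 0 | 0 | 0 | 0 | 0 |
| 0.25 | 0.33 | 0.33 to 2.67 | 3 | 7 | 13 |
| 0.50 | 1 | 1 to 8 | 10 | 20 | 40 |
| 0.75 | 3 | 3 to 24 | 30 | 60 | 120 |

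At e = 0.10 the three non-zero ratios are 0.10 × 0.333/0.5 = 0.067, 0.10 × 1/0.5 = 0.20 and 0.10 × 3/0.5 = 0.60. Against a 25% rebate they double, to 13%, 40% and 120%. As an example, M = SGD30 and s = 0.50 give 0.10 × 30 × 1 = SGD3 per month omitted, against a rebate of 0.5 × 30 = SGD15. If e = 0, every entry is zero.

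**4. What the percentages are not.** They compare the omitted subsidy with a rebate on the drugs alone. The real rebate base also includes a visit, which lowers the ratio. Patients below 75% adherent days earn no rebate, which raises the ratio to the mean incentive per VP patient. The ICER would rise by a smaller percentage than incentive cost does, because operating and administrative costs are also in the numerator; the protocol gives no figure for them.

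**The case against.** The strongest case against is that the perspective and the cost list can be read as consistent. The rebate is itself a subsidy of out-of-pocket costs. If the agency is simply whoever would fund the rebate at scale, then incentives plus running costs are its full programme cost. The wording allows this reading, which is why restating the perspective is an acceptable repair. It does not settle the matter as written, because an agency described as subsidising healthcare costs would ordinarily bear changes in that care.

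It can also be said that an article condenses detailed costing. That is fair for unit prices and methods. But the article states where the costs will come from, and that rule does not match the viewpoint in the sentence that follows it.

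Several stronger readings are tempting, and the document does not support them.

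- **The ICER is definitely biased in favour of VP.** The protocol never says that eye drops are subsidised. If they are not, nothing is omitted on medication.
- **The more effective the rebate, the more cost is left out.** An adherent day requires every dose inside its window, so the measure can improve through timing alone. The Explanatory outcomes treat doses taken regardless of timing as a separate quantity.
- **The error can only go one way.** The cost list also leaves out possible savings in other care, such as counselling or surgery. The Discussion calls the trial probably too short to show differences in progression, so offsets within it are likely small. That makes understatement the likelier direction but does not prove it.
- **The omission is 11%, 33% or 100% of the rebate.** A reader would get these figures by assuming adherence rises from 60% to 70% and using 10/60 for e. The rebate base is a full three-month supply, so a 10-point rise is 0.10 of that base and the ratios are 7%, 20% and 60%.
- **Bills give a complete purchase record.** Patients are asked to bring them for a check on gaming. The protocol does not say that quantities are recorded for every patient.

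**Conclusion.** The point holds conditionally. The stated cost rule leaves out between-arm changes in government-paid medication and visits that the stated perspective would include, and the rebate formula does not make up for it. If drops are subsidised and VP increases the quantity used, VP's incremental cost is understated, and the ICER with it, unless savings in other subsidised care offset the difference.

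The size cannot be fixed from the protocol. With an assumed 10-point rise in doses used, it is about 7%, 20% or 60% of a 50% rebate on the same drugs at assumed subsidy shares of 25%, 50% or 75%, and nil without a subsidy or without extra use. So it may be negligible or a substantial part of the incentive cost.

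The importance is minor. The ICER is a secondary analysis, run only if both quality-of-life scores improve, and the primary adherence result does not depend on it.

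**What to change.** Add to the cost definition the between-arm difference in government-paid glaucoma medication and visit costs.

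- Take medication quantities from doses taken regardless of timing, which is already an explanatory outcome. Check them against the month 6 bills where patients bring them.
- Because the subsidy share is not in the protocol, report the ICER with and without this line over a stated range of shares, including zero.

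Alternatively, restate the perspective as that of the rebate payer only, and say that changes in subsidised care are outside it.

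The cost is one more line in the economic analysis, some data entry from bills where they are available, and possibly a less favourable ICER. No change to the intervention, the sample size or the primary analysis is needed.
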